### Primary outcome

The estimate corresponding to the primary estimand of the NPI-Q severity of the PwD at 90 days will be obtained from a likelihood-based longitudinal data analysis model, with responses consisting of all scores (baseline, 90 and 180 days post-randomisation) [14]. The model will include factors representing intervention (SC, MI + SC, RI + SC), time, intervention by time interaction with the restriction of a common baseline mean score across interventions and unstructured variance–covariance among repeated measurements. The model will adjust for the stratification variable (site) used during the randomisation and will be referred to as the unadjusted model. Recruitment site includes Northern Australia, Southern Australia, Norway, the UK, Poland and Germany. The model will include the SC alone group as the reference group.

In sensitivity analysis, variables known to be prognostic of NPI-Q severity (i.e. type of dementia, gender of PwD and CG’s relationship with PwD) will be included in the unadjusted longitudinal data analysis model. This model will be referred to as the adjusted model. The treatment effect estimated from the unadjusted and adjusted models will be the mean difference in NPI-Q severity from baseline to 90 days post-randomisation between the MI plus SC versus SC alone groups.

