### Sample size

The trial was designed to recruit a total of 495 dyads (165 per arm) to detect a difference of 3 points in NPI-Q total severity score between the MI plus SC and SC alone at 90 days post-randomisation. This assumes 90% power, a two-tailed significance level of 5%, an equal standard deviation of 7.5 points in the groups, no correlation between baseline and 12 weeks (conservative) and 20% attrition. A 3-point change from baseline in NPI-Q total severity score is considered a clinically meaningful difference [11]. No interim analyses to stop the trial early were planned, and no interim analysis was conducted.

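### The primary model is valid but leaves out three baseline variables the plan itself calls prognostic, giving up a modest amount of precision that could be had almost free before unblinding

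*SAP article*

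**What the plan says.** Under Primary outcome, the primary estimate comes from a likelihood-based longitudinal model of NPI-Q severity at baseline, 90 and 180 days. It has terms for intervention and time and an "intervention by time interaction with the restriction of a common baseline mean score across interventions". On covariates: "The model will adjust for the stratification variable (site) used during the randomisation and will be referred to as the unadjusted model". The second model is described next: "In sensitivity analysis, variables known to be prognostic of NPI-Q severity", namely type of dementia, gender of the person with dementia and the caregiver's relationship, are added to the first model, and the result is called the adjusted model. Both models are said to estimate the same mean difference, music plus standard care against standard care alone at 90 days.

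Four other sections bear on the point:

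- **Randomisation** stratifies by site only.
- **Baseline dyad characteristics** lists dementia diagnosis, sex and the caregiver's relationship among the variables summarised by arm, so all three are collected.
- **Subgroup analyses** already defines the categories of all three, with a level for other or unknown dementia type.
- **Multiple testing** allows the music versus reading test if music versus standard care gives p < 0.05 at 90 days. It does not name the model, but read with Primary outcome it is the site-only one.

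**The concern.** The plan asserts that three baseline variables predict the outcome, then leaves them out of the model that decides the trial, and gives no reason. For a mean difference in a linear model, adding baseline covariates leaves the target unchanged and removes residual variance. The plan therefore has two models for one estimand, and the one expected to be less precise decides. If the two fell on either side of 0.05, the site-only result would settle both the primary claim and whether music versus reading may be tested.

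Two things are at stake: the width of the primary interval, and how the result behaves if the arms happen to differ on one of these variables. Nothing in the randomisation balances them beyond chance.

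**Working it through.** **1. The plan's own sample size.** Inputs from Sample size: difference 3 points, "an equal standard deviation of 7.5 points in the groups", two-sided 5%, power 90%, attrition 20%. 

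n per arm = 2 × 7.5² × (1.960 + 1.282)² / 3² = 131.3, rounded up to 132. Then 132 / 0.80 = 165 per arm and 3 × 165 = 495. This matches the stated figure. The calculation assumes zero correlation with baseline, so planned power relies neither on the three variables nor on the baseline score.

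**2. Variance removed by the three variables.** Let ρ be the baseline to day-90 correlation, and let R² be the share of variance the three variables explain at each visit, with the same effect at both. The documents give neither value. I assume ρ = 0.3–0.6 and R² = 5–15%. With unit variance and site ignored:

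- Day-90 residual variance given baseline (the primary model): 1 − ρ².
- Given baseline and the three variables: (1 − R²) − (ρ − R²)² / (1 − R²).

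For ρ = 0.3 and R² = 15%: 0.85 − 0.15²/0.85 = 0.8235, against 1 − 0.09 = 0.91. The ratio is 0.905. The interval scales with √0.905 = 0.951, so it is 4.9% narrower.

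The equivalent number of extra dyads in the two arms is 330 × (1/ratio − 1). Power is from the noncentral t with 132 per arm, a 3-point difference and SD 7.5 × √(residual variance).

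| ρ | R² | Variance ratio | CI narrower by | Extra dyads (of 330) | Power without → with |
|---|---|---|---|---|---|
| 0.3 | 5% | 0.972 | 1.4% | 10 | 92.4% → 93.1% |
| 0.3 | 15% | 0.905 | 4.9% | 35 | 92.4% → 94.6% |
| 0.5 | 10% | 0.963 | 1.9% | 13 | 96.2% → 96.8% |
| 0.6 | 5% | 0.987 | 0.7% | 4 | 98.2% → 98.3% |
| 0.6 | 15% | 0.956 | 2.2% | 15 | 98.2% → 98.5% |

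In the middle case (ρ = 0.5, R² = 10%), the 95% half-width 1.96 × 7.5 × √(0.75 × 2/132) = 1.57 points becomes 1.54.

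If R² is instead defined as variance explained beyond baseline, the ratio is simply 1 − R², and 5–15% narrows the interval by 2.5–7.8%. The table uses the more cautious definition.

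**3. Validity with the variables omitted.** A null simulation (40,000 runs, 132 per arm, one omitted covariate with R² = 10%, plain two-sample t-test without baseline) rejected in 4.9% of runs. Split by observed standardised imbalance, rejection was 3.8% below 0.5 and about 10% above 2. The latter covers under 5% of runs. The effect is therefore conditional only.

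**4. Size of the conditional effect.** An imbalance of 1.96 standard errors in the combined prognostic score shifts an estimate that ignores baseline by 7.5 × √R² × 1.96 × √(2/132). That is 0.40 points at R² = 5% and 0.70 at 15%. Under the assumptions of step 2, the common-baseline constraint multiplies the shift by (1 − ρ):

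- R² = 5%, ρ = 0.6: 0.40 × 0.4 = 0.16 points.
- R² = 15%, ρ = 0.3: 0.70 × 0.7 = 0.49 points.

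The design difference is 3 points.

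**The case against.** The strongest reply is that nothing here is wrong. Both models are pre-specified and ranked. Adjusting the primary model for baseline and the stratification factor, with further covariates in a supporting analysis, is a legitimate choice. The trial was sized without counting on any covariate gain, and at the planned size the existing model exceeds 90% power in every scenario above. The adjusted estimate will be reported, so readers will see whether imbalance moved the result. All of this stands, and it limits the point to one of efficiency.

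A reader might infer three stronger things, and the document supports none of them:

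- *That the primary p-value is biased or its error rate inflated.* Step 3 shows otherwise. Exposure to imbalance exists only given the imbalance observed, and the constrained baseline removes part of it.
- *That the adjusted model tests nothing and is mislabelled as a sensitivity analysis.* The section on missing data assumes missingness at random given observed data in the model. Adding three variables changes what is conditioned on, so comparing the models does probe that assumption.
- *That the trial is underpowered without these variables.* The stated sample size reproduces without them.

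The objection also notes that the change would come after follow-up ended. That matters less. The Introduction and Trial status sections keep the plan open to tracked changes until it is signed before the code is broken, and this change can be made without sight of allocation.

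**Conclusion.** The point holds as a modest efficiency weakness, not an error or a contradiction. Having declared three collected variables prognostic, the plan gives no reason for keeping them out of the deciding model. Over the assumed ranges the loss is about 1–10% of residual variance, 0.7–5% of interval width, and at most about two points of power at the planned size (92.4% to 94.6%). If the variables explain less than 5%, the gain is smaller still. Validity and unbiasedness are not in question. The figures rest on assumed R² and ρ, equal covariate effects at both visits, and 132 evaluable dyads per arm. The article does not state actual enrolment.

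Separately, *unadjusted* is the wrong name for a model that adjusts for site and, through the common baseline, for baseline NPI-Q. The Secondary outcomes and Subgroup analyses sections carry that label forward.

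**What to change.** Before the allocation code is broken:

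1. Make the primary analysis the longitudinal model with site plus type of dementia (in the Subgroup analyses categories), gender of the person with dementia and caregiver's relationship, each with its own effect at each visit.
2. State under Multiple testing that this model's p-value opens the music versus reading test.
3. Report the site-only model as supportive, and rename it wherever it is called unadjusted, for example as the site-adjusted model.
4. Add one rule for a missing baseline covariate, applied without reference to arm. Dementia type already has an unknown level; gender and relationship do not.

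If the sponsor prefers to keep the site-only model primary, the SAP should say why.

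The cost is SAP wording, with no new data or participants. Dementia type (three levels), gender (two) and relationship (three) add 2 + 1 + 2 = 5 terms per visit, or 15 mean parameters over three visits, which is small against the planned 495 dyads.

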### Secondary outcomes

Secondary outcomes for the PwD and CG will be analysed similarly to the primary outcome at 90 days and 180 days (where applicable) post-randomisation. The treatment effect will be obtained unadjusted as the mean difference from baseline to post-randomisation between the groups MI plus SC versus SC alone and MI plus SC versus RI plus SC. Appropriate transformations may be applied to the variables before fitting the model if considered skewed.

### Safety outcomes

The number and percentage of PwD and CGs who experience adverse events will be summarised across the intervention period (i.e. randomisation to 90-days post-randomisation), the follow-up period (i.e. 90-days post-randomisation to 180-days post-randomisation) and study period (i.e. randomisation to 180 days post-randomisation) by each intervention group. The total number of events will be reported for the PwD and CG separately.

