**Interventions:**							
***Music intervention training***			X	X	X		
***Reading intervention training***			X	X	X		

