### Analysis populations

The analysis set will consist of all dyads who were randomised, with all dyads reported and analysed according to their randomised study arm. The safety population will consist of all dyads receiving at least one study treatment (including SC alone), with all dyads reported and analysed according to the intervention received. Participants in the MI or RI arms will be considered as having received the study treatment if the dyad attended at least one training session and that all training components were delivered (meeting the fidelity criteria).

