## Effectiveness analysis

### Primary estimand

The estimand for HOMESIDE is defined according to the addendum to the ICH E9 on estimands and sensitivity analysis in clinical trials [13]. HOMESIDE aims to answer the specific research question: does the addition of music therapy to SC in a home setting delivered by a CG to PwD, compared to SC alone over 90 days, improve BPSD of the PwD, as measured by the mean difference in NPI-Q severity, regardless of the post-randomisation (intercurrent) events listed below, while assigning the worst possible NPI-Q score to the PwD who died.

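### The safety table counts events from randomisation but admits MI and RI dyads only after training, so it leans, slightly if the first session qualifies, towards the active arms

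*SAP article*

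**What the plan says.** Three parts of the SAP article bear on this.

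- **Clock.** Safety outcomes (under Effectiveness analysis) summarises adverse events "across the intervention period (i.e. randomisation to 90-days post-randomisation", with further windows for follow-up and for the whole "study period (i.e. randomisation to 180 days post-randomisation) by each intervention group". Time zero is randomisation in every arm.
- **Entry and arm.** Analysis populations states: "The safety population will consist of all dyads receiving at least one study treatment (including SC alone". Arm membership in this set follows what was delivered, not the allocation: "with all dyads reported and analysed according to the intervention received". An MI or RI dyad counts as treated only if it "attended at least one training session and that all training components were delivered". SC has no equivalent step, since those caregivers simply continue usual care.
- **Timing of training.** Table 1 marks "Music intervention training" and the corresponding reading training at days 1, 21 and 42. The Adherence section allows that the first session fell at the end of week 1 for some dyads.

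The effectiveness analysis works differently. It uses all randomised dyads in their randomised arm, "while assigning the worst possible NPI-Q score to the PwD who died". Primary estimand attributes also lists death and hospitalisation of either member of the dyad as intercurrent events, to be described overall and by treatment arm.

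**The concern.** An MI or RI dyad must get through some time after randomisation, alive and able to be trained, before it can belong to its arm's safety table. An SC dyad belongs from day 0. If a death, or an illness that rules out training for good, occurs in that gap, it cannot appear under MI or RI. The safety set is defined by intervention received and SC alone is named as a treatment, so such a dyad is either outside the set or reported under SC. The article does not say which. The same event in an SC dyad is always counted.

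Both routes push the percentages in one direction. With no true difference, MI and RI look a little safer than SC. At stake is the between-arm reading of the adverse-event table, chiefly its serious events (hospitalisations or deaths).

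**Working it through.** **Arm size.** From Sample size: difference 3, SD 7.5, two-sided 5%, 90% power, 20% attrition. n = 2 × (1.960 + 1.282)² × 7.5² / 3² = 131.3, so 132 per arm. 132 / 0.80 = 165, and 3 × 165 = 495. The plan's figure reproduces and is not in dispute. It only supplies N = 165.

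**Assumptions.** The article gives no event rates and no actual training delays. I assume a 90-day death risk r, the same in all arms, at a constant hazard, and qualifying training on day t. The true MI/SC ratio is then 1.00.

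**Formulas.**
- Hazard: h = −ln(1 − r) / 90.
- Probability of death before qualifying: e = 1 − exp(−h·t).
- Deaths affected per active arm: 165·e.
- Apparent MI risk: (r − e) / (1 − e).
- Apparent SC risk: r if the early MI and RI deaths are dropped, or (r + 2e) / (1 + 2e) if those from both active arms are counted under SC.

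**Worked case, r = 3%, t = 7.** h = 0.03046 / 90 = 0.000338, so e = 0.00237 and 165·e = 0.39. MI risk = 0.02763 / 0.99763 = 2.77%. SC risk = 3.00% (dropped) or 0.03473 / 1.00473 = 3.46% (moved). The ratios are 2.77 / 3.00 = 0.92 and 2.77 / 3.46 = 0.80.

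**Results for r = 3%.**

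| Entry day | Deaths affected per active arm | Share of 90-day deaths | MI risk | SC risk, dropped / moved | Ratio, dropped / moved |
|---|---|---|---|---|---|
| 1 | 0.06 | 1% | 2.97% | 3.00% / 3.07% | 0.99 / 0.97 |
| 7 | 0.39 | 8% | 2.77% | 3.00% / 3.46% | 0.92 / 0.80 |
| 42 | 2.33 | 47% | 1.61% | 3.00% / 5.66% | 0.54 / 0.28 |

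**Sensitivity to r.** Over r = 1% to 10% the ratios hardly move: 0.99 / 0.97 at day 1, 0.92–0.93 / 0.80–0.81 at day 7, and 0.53–0.55 / 0.28–0.31 at day 42. The number of deaths scales with r. At 5% it is 0.09 (day 1), 0.66 (day 7) and 3.90 (day 42) per active arm.

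**Which row applies.** It depends on what the delivery of all training components means. If it refers to the components of one session, entry is at day 1 to about day 7. If it refers to the whole programme, entry is at day 42. The requirement of at least one attended session fits the first reading better, but the wording does not exclude the second.

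**Non-fatal events.** A dyad with a hospitalisation before training that is trained later enters MI or RI. Because the clock starts at randomisation, that event is counted. Only events after which qualifying training never happens are lost or moved.

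**The case against.** The strongest reply is that the early deaths remain visible elsewhere. Primary estimand attributes describes deaths and hospitalisations by treatment arm as intercurrent events, under an estimand analysed on all randomised dyads, and the CONSORT diagram reports withdrawals and losses with reasons. Safety is only summarised, with no test and no planned risk ratio. On the first-session reading the expected effect is a fraction of one death: with a Poisson mean of 0.39 an active arm has about a 68% chance of no affected death, and with 0.06 about 94%. Counting under SC is an inference, because the article does not place untrained dyads anywhere. An as-received safety set beside an as-randomised effectiveness set is also common, so differing death counts between the two are not in themselves a contradiction. Finally, the Safety outcomes section does not itself name the safety population, although that set has no other evident use in the article.

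All of this stands and limits the size of the point. It does not remove the asymmetry. The intercurrent-event description counts dyads under a 90-day estimand. It does not replace the adverse-event table, which reports each member of the dyad and runs to day 180. In that table the entry rule still works in one direction only.

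**Conclusion.** The point holds as a minor one. Followed as written, the entry rule and the clock together leave deaths, and other events that permanently prevent training, out of MI and RI (or possibly move them to SC) while always counting them in SC. If the first session qualifies, the effect is well under one expected death per active arm at risks up to 5%. The size rests on assumed mortality, a constant hazard equal across arms, the planned 165 per arm and the assumed entry day.

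A reader might infer more: that the trial's only safety comparison is heavily biased, that early deaths disappear altogether, or that hospitalisation percentages are distorted generally. The documents do not support this. Deaths and hospitalisations are also described by arm as intercurrent events, and non-fatal events followed by later training are kept. The ratios of about 0.28 to 0.54 need the whole-programme reading of the entry rule. The primary effectiveness analysis is not touched.

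**What to change.** In Analysis populations and in Safety outcomes:

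1. Make the main safety table all randomised dyads, by randomised arm, counted from randomisation. Under equal hazards the ratio is then 1.00 whatever the training delay.
2. Check that its deaths and hospitalisations agree with the intercurrent-event counts, and its deaths of persons with dementia by day 90 with those scored 36 in the primary analysis.
3. Keep the as-received table as supportive. State where MI and RI dyads without qualifying training are reported, and whether the training components meant are those of one session or of the whole programme.

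The cost is SAP wording and one more set of tables from data already held. The downside is that the main table will include a few dyads who never received the intervention, which the supportive table addresses. The article allows tracked changes up to unmasking and treats later ones as post hoc, so the change belongs in the version signed at the masked data review.

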### Concurrent medications

The type of medications (analgesics, antipsychotics, antidepressants, anti-dementia drugs, anti-epileptics, anti-Parkinson’s, anxiolytics, corticosteroids, hypnotics and sedatives, other nervous system drugs) that the PwD and CG were taking at baseline, 90 and 180 days post-randomisation and study period will be summarised by each intervention group across the intervention period (i.e. randomisation to 90-days post-randomisation), the follow-up period (i.e. 90-days post-randomisation to 180-days post-randomisation) and study period (i.e. randomisation to 180 days post-randomisation.

### Subgroup analyses

Exploratory subgroup analyses will be performed for the primary outcome, NPI-Q severity at 90 days and 180 days post-randomisation. The following subgroups will be explored: (i) gender of PwD (male, female); (ii) gender of CG (male, female); (iii) type of dementia (neurodegenerative diseases [Alzheimer’s disease, frontotemporal dementia, Lewy body disease], mixed [vascular dementia, mixed dementia], other [other or unknown]); (iv) severity of dementia of PwD at baseline (no cognitive impairment [MMSE score of 24–30], mild cognitive impairment [19–23], moderate cognitive impairment [10–18], severe cognitive impairment [< 10]); (v) time of onset dementia (early [under 65 years old] vs late [≥ 65 years old]); (vi) length of time PwD has had dementia (years); (vii) CG’s relationship to PwD (spouse or partner, child or other [sibling, friend, other]); and (viii) country (Australia [Northern Australia and Southern Australia combined], Norway, the UK, Poland, Germany).

For each subgroup analysis, the subgroup (main effect) and its interaction with the intervention group at each time point will be included in the unadjusted longitudinal data analysis model. This will enable the evaluation of whether the treatment effect differs between subgroup categories. Results of the subgroup analyses will be displayed using forest plots, presenting the estimate and two-sided 95% CI of the treatment effect within each subgroup level and the *p*-value of the interaction test. For the length of time that the PwD has had dementia, we will present the between-group difference in the mean change in NPI-Q severity visually, including the 95% confidence intervals.

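### The subgroup model lists no subgroup-by-time term; fitted from that list with SC as reference, differences in symptom course shared by all arms would show up largely as treatment-by-subgroup interaction

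*SAP article*

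**What the plan says.** The Primary outcome section builds the base model from intervention (three levels), time, and an "intervention by time interaction with the restriction of a common baseline mean score across interventions". It uses an unstructured covariance and adjusts for site; the responses are the baseline, 90-day and 180-day scores. It adds: "The model will include the SC alone group as the reference group".

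The Subgroup analyses section then extends this model. For each subgroup variable, "the subgroup (main effect) and its interaction with the intervention group at each time point will be included". The output is a set of forest plots "presenting the estimate and two-sided 95% CI of the treatment effect within each subgroup level", with an interaction p-value. Length of time with dementia is kept continuous and shown graphically. The status is stated openly: "Exploratory subgroup analyses will be performed for the primary outcome, NPI-Q severity at 90 days and 180 days post-randomisation".

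**The concern.** In a constrained model with SC as reference, the SC course is carried by the time effect, and intervention enters as the MI and RI contrasts at 90 and 180 days. Adding a subgroup main effect, which is constant over the three visits, and the subgroup interaction with those contrasts leaves SC with the same change over time in every subgroup. Suppose one subgroup worsens, or regresses towards the mean, faster than another in all three arms alike. The SC part of the model cannot follow it; the MI and RI interaction terms can.

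At stake are the interaction p-values and the within-level effects in the forest plots, which would mix prognosis with effect modification. Several of the subgroup variables (baseline MMSE, type of dementia, age at onset, duration) are ones whose NPI-Q course could plausibly differ. The Primary outcome section itself calls type of dementia, gender of the person with dementia and the caregiver's relationship prognostic of NPI-Q severity. That is a statement about level, not course, so it suggests a difference in course without establishing one.

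**Working it through.** **Plan's own figure.** From the Sample size section: difference 3, SD 7.5, two-sided 5%, power 90%, attrition 20%. n = 2 × (1.960 + 1.282)² × 7.5² / 3² = 131.3, so 132 per arm; 132 / 0.80 = 165; 3 × 165 = 495. This reproduces the plan. The article gives no figure for the subgroup model.

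**Inputs.** 132 completers per arm and SD 7.5, from the plan. Assumed, because the article does not give them: two equal subgroups (66 and 66 per arm); equal correlation ρ between visits, from 0 (the plan's planning value) to 0.7; a course difference of g points at both 90 and 180 days, the same in all arms; no true treatment-by-subgroup interaction.

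**Model fitted from the listed terms, SC as reference.** The subgroup difference in one arm at one visit has variance v = 7.5² × (1/66 + 1/66) = 1.705.

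1. *Main effect b.* SC supplies three correlated subgroup differences (0, g, g), all modelled as b: mean 2g/3, information 3/(1+2ρ) in units of 1/v. MI and RI have free follow-up terms, so each informs b only through its baseline difference of 0, with information 1. Hence b = [2g/(1+2ρ)] / [3/(1+2ρ) + 2] = 2g/(5+4ρ).
2. *False interaction at 90 days.* The fitted MI subgroup difference is g + ρb, because the baseline misfit carries forward through ρ. Subtracting b gives g − (1−ρ)b = g(3+6ρ)/(5+4ρ). The shortfall from g arises because the main effect absorbs part of the course difference.
3. *Standard error.* SE² = v[(1−ρ²) + (1−ρ)²(1+2ρ)/(5+4ρ)].
4. *Rejection.* Φ(−1.96 − est/SE) + 1 − Φ(1.96 − est/SE). Example at ρ=0.5, g=2: estimate 1.714, SE 1.183, ratio 1.449, rejection 30.5%.

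| ρ | False estimate | SE, listed terms | g=1 | g=2 | g=3 | SE, subgroup-by-time added |
|---|---|---|---|---|---|---|
| 0 | 0.60g | 1.43 | 7.0% | 13.4% | 24.2% | 1.85 |
| 0.3 | 0.77g | 1.33 | 9.0% | 21.4% | 41.6% | 1.76 |
| 0.5 | 0.86g | 1.18 | 11.2% | 30.5% | 58.4% | 1.60 |
| 0.7 | 0.92g | 0.96 | 16.1% | 48.7% | 82.4% | 1.32 |

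At g=0 the estimate is unbiased and rejection is 5%.

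**With subgroup by time added.** The MI and SC follow-up differences are each free, so g cancels: expected estimate 0, SE² = 2v(1−ρ²), rejection 5.0% for every g and ρ tried.

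**Other reading of the sentence.** Giving every arm, SC included, its own subgroup term at each follow-up visit yields the same estimate and SE as adding subgroup by time.

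**Checks.**
- Simulation, 600 runs, estimated unstructured covariance, ρ=0.5. Listed terms: g=2 bias 1.81, rejection 33.7%; g=3 bias 2.61, rejection 57.0%. With subgroup by time: bias 0.05 and 0.03, rejection 5.8% and 4.8%.
- A 30:70 subgroup split leaves the bias unchanged; rejection at g=2, ρ=0.5 is 26.4%.
- If the course difference at 180 days is twice that at 90 days (2 points at 90), rejection is 16.9%, 26.4% and 45.6% at ρ = 0.3, 0.5 and 0.7.

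**How large might g be?** The article does not say. One rough illustration uses its entry threshold of 6 on the NPI-Q. Take two subgroups with assumed normal scores, SD 7.5 and underlying means 8 and 12. Truncation at 6 raises the mean baseline score by about 4.8 and 2.8 points, a gap of 2.0. Regression to the mean then gives g ≈ 2.0 × (1−ρ), or about 1.4, 1.0 and 0.6 at ρ = 0.3, 0.5 and 0.7. The larger values of g would need a real difference in disease course as well.

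**The case against.** The strongest reply is that the sentence need not mean what the literal list says. The Primary outcome section defines intervention as a three-level factor that includes SC. Interacting subgroup with that whole factor at each follow-up visit includes SC by subgroup by time, and so contains the term in question. Naming SC as reference fixes which contrasts are reported; it does not by itself exclude that coding. Nor are the article's term lists exact parametrisations: taken strictly, an interaction at each time point would include baseline, where arm differences are constrained away. This stands. A reader might infer that the plan definitely omits the term, and the text does not support that. It leaves two codings open, only one of which is safe. Against the reply, the base model spells out its lower-order terms and the subgroup sentence labels its main effect, so an analyst working from the list could reasonably fit only what is there.

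Three further points stand. The bias is conditional on a course difference that the article nowhere quantifies, and g=3 equals the whole treatment difference the trial was sized to detect. At the plan's own planning correlation of 0, rejection is 7.0%, 13.4% and 24.2%, well below the figures at higher correlations. The subgroup results are labelled exploratory and, under Multiple testing, are left unadjusted for readers to weigh.

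**Conclusion.** The point holds in conditional form. The subgroup-by-time term is not stated. If the constrained model is fitted from the listed terms with SC as reference, 60% to 92% of any course difference shared by all arms (ρ from 0 to 0.7) enters the MI-by-subgroup estimate at 90 days, and the nominal 5% test rejects in about 7-16%, 13-49% and 24-82% of trials for g of 1, 2 and 3 points. These figures rest on 132 completers per arm, SD 7.5, two equal subgroups, the same g at both follow-up visits and no true interaction. With equal subgroups, symmetry puts half the false interaction on each level in the forest plot: about −0.86 and +0.86 points at g=2, ρ=0.5.

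A reader might go further and conclude that the planned subgroup p-values and forest plots are biased. The article does not support that: the alternative coding removes the problem, and so does g=0. The primary and secondary analyses do not use this model and are unaffected. What remains is more than missing detail, because one natural way of following the sentence gives an invalid interaction test.

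**What to change.** Replace the sentence with: subgroup, subgroup by time, and subgroup by intervention by time (90 and 180 days) will be added to the unadjusted longitudinal model; the interaction p-value is the test of the three-way terms for MI plus SC versus SC at the stated time. For continuous duration of dementia, add duration by time and duration by intervention by time in the same way.

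The cost is two extra parameters per non-reference subgroup level (eight for the five-level country variable) and a larger interaction standard error, for example 1.18 to 1.60 at ρ=0.5 with equal subgroups. The smaller figure is obtained only by assuming that SC courses are parallel. The article allows tracked changes until the code is broken and calls later ones post hoc, so the clarification belongs in the signed SAP. If unmasking has already taken place, it should be reported as a post hoc clarification of the model.
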